### Intervention

2.5

Meals for this study will be provided by the MANNA, a Philadelphia-based nonprofit organization that prepares and delivers MTMs for individuals with serious illnesses, including cancer. MANNA's MTM program aligns with evidence-based nutrition guidelines while accommodating medical diagnoses and select dietary preferences. Meals are developed collaboratively by Registered Dietitian Nutritionists (RDNs) and professional chefs and prepared onsite in MANNA's commercial kitchen using fresh, nutrient-dense ingredients. For this study, MANNA will provide kid-friendly, ready-to-eat/heat meals that are aligned with oncology nutrition guidelines and designed to support adequate energy and protein intake. Dietary restrictions that cannot be accommodated by MANNA are assessed during enrollment to ensure appropriateness.

Once participants are enrolled in the study, their information will be transmitted to MANNA via a standardized referral form completed by the study team. This referral is sent to MANNA's Client Services Department, which then assumes responsibility for onboarding families into the MTM program. A MANNA representative contacts the caregiver directly to initiate services and schedule meal delivery. During this intake call, caregivers are asked about dietary restrictions, food preferences, and medical considerations; accommodations are made when feasible and consistent with MANNA's available diet modifications. Dietary preferences and restrictions may be updated throughout the study period as needs change. Families select a preferred weekly delivery day, and adjustments to upcoming deliveries can be accommodated if requested at least two days prior to the scheduled delivery. At the start of service, families receive a MANNA-provided booklet outlining safe storage and reheating instructions, as well as contact information for questions, concerns, or troubleshooting. Caregivers may request changes to meal frequency (e.g., temporary reduction in meals) at any time, and all change requests can be communicated either directly to MANNA or through study staff, who will coordinate with MANNA to ensure continuity of services and alignment with study procedures.

*From Kitchen to Clinic* is a family-centered, food-as-medicine intervention combining MTMs and caregiver coaching with the goal of reducing treatment-related barriers to healthy eating and supporting families during a critical early period following diagnosis. The intervention is delivered over a 12-week period and consists of two phases: an intensive phase (weeks 1–8) followed by a tapered phase (weeks 9–12). During the intensive phase, participating families will receive a higher frequency of medically tailored meals to provide consistent nutritional support during the early, most treatment-intensive period following diagnosis. In this phase, families will receive a weekly delivery of 21 pre-cooked meals (7 breakfasts, 7 lunches, 7 dinners, healthy desserts, and fruit) for the pediatric patient, and 7 meals per week provided for the family to use as they desire (families are also able to opt-out of the 7 family meals, and those data will be included in our feasibility and acceptability analyses). Caregivers will also receive weekly one-on-one coaching sessions (remote or in-person, depending on caregiver preference) with a RDN. Sessions will focus on building caregiver skills, knowledge, and confidence in providing nutrition support, managing treatment-related challenges, and incorporating MTMs into family routines.

During the tapered phase (weeks 9–12), the frequency of meal delivery and coach contact will be reduced to support transition toward greater caregiver autonomy and sustainability of dietary behaviors beyond the intervention period. During this phase, families will receive a weekly delivery of 7 meals (1 meal per day) for the pediatric patient, while family meal support remains consistent (7 per week). Caregiver coaching will transition to bi-weekly sessions, providing continued support while encouraging autonomy. This stepped-down approach is intended to balance ongoing support with skill-building and prepare families for independent meal planning as treatment routines stabilize.

### Data collection schedule

2.6

Data will be collected at four primary time points: baseline (prior to or at initiation of the intervention), and post-intervention follow-up at 3, 6, and 12 months. Baseline assessments will occur after informed consent and assent are obtained and before delivery of intervention components. Post-intervention assessments will be conducted immediately following completion of the intervention period, and follow-up assessments will be conducted to evaluate short-term maintenance and feasibility of continued data collection. Feasibility metrics, including recruitment, retention, adherence to intervention components, assessment completion, and intervention engagement, will be tracked continuously throughout the study. Data collection at baseline, 3, 6, and 12 months will include patient dietary intake, weight outcomes, and treatment tolerance; household food and nutrition security; and caregiver burden and distress. The timing and burden of assessments will be monitored to inform optimization of the protocol for future trials. See Table 1 for the schedule of procedures.

**Table 1 tbl1:** Schedule of study procedures.

Study Activity	aScreening/Enrollment	Intervention Period			Follow-up Period		
		aBaseline (+14 days)	aWeek 1-8 (Intensive)	aWeek 9-12 (Transition	a3 Month (+28 days)	a6 Month (±28 days)	a12 Month (±28 days)
Eligibility screening	X						
Informed consent/assent	X						
Medical record review	X	X	X	X	X	X	X
Anthropometrics: height, weight, BMI z-score		X			X	X	X
Mid-upper arm circumference (MUAC)		X			X	X	X
Medically Tailored Meals		X	$X^{1}$	$X^{1}$			
Caregiver Coaching Session			$X^{2}$	$X^{2}$			
Caregiver Personal Characteristics survey		X					
Challenges and Goals survey		X					
Resources and Preferences for Supportive Care survey		X					
Caregiving Experience survey		X					
Meals and Meal-time Behaviors survey		X					
Food Security survey		X			X	X	X
Healthfulness Choices survey		X			X	X	X
Nutrition Security survey		X			X	X	X
PROMIS Emotional Distress – Anxiety survey		X			X	X	X
PROMIS Satisfaction with Social Roles/Activities survey		X			X	X	X
Intervention Acceptability survey					X		
Meal Adherence survey			$X^{3}$	$X^{3}$			
Adverse Event Reporting			X	X	X	X	X
Child Dietary Intake (ASA24)		$X^{4}$			$X^{4}$	$X^{4}$	$X^{4}$
Healthy Eating Index (HEI-2020)		$X^{5}$			$X^{5}$	$X^{5}$	$X^{5}$

1: MTM- 21 meals for patient, 7 meals for family per week; weekly caregiver one-on-one coaching session.

2: MTM- 7 meals for patient, 7 meals for family per week; bi-weekly caregiver one-on-one coaching session.

3: Caregiver will complete survey weekly during the intervention period.

4: Via caregiver proxy; 3 recalls: 2 weekday, 1 weekend.

5: Scored form ASA24.

a The study activities do not need to occur on the same day based on visit type.

### Outcomes

2.7

The feasibility, acceptability, and intervention adherence outcomes described below and outlined in Table 1, Table 2 are the primary outcome measures being assessed in this feasibility study. To characterize the sample, self-report information will be collected regarding race, ethnicity, sex, gender, income, education, child diagnostic and treatment information, and caregiving characteristics. Clinical and demographic information will be abstracted from participant charts by the study team. Information that is not collected as part of routine care will be obtained directly from the caregiver.

**Table 2 tbl2:** Feasibility and acceptability progression criteria.

Outcome	Measure	Criteria
Recruitment feasibility	Participants enrolled per month of recruitment	≥3 dyads/month
Retention feasibility	Percent of participants providing assessment data at 12 weeks	≥75%
Assessment feasibility	The proportion of retained participants who provide valid data for each assessment task	≥85%
Intervention acceptability	Intervention acceptability survey Domains: Items grouped into three subscales: Meals Acceptability (items 4–8) Coaching Acceptability (items 9–12) Overall Program Acceptability & Integration (items 1–3, 13–15) *See Table 3 for details	Median score ≥4
Intervention adherence (Coaching and MTM adherence)	Caregiver coaching adherence (dose received): Attendance rate	≥75% of coaching sessions completed
	Child and family meals consumed will be assessed using three complementary sources: 1. Weekly 3-item caregiver survey Categorical (weeks 1-8) and numeric (weeks 9-12) responses converted to weekly MTM uptake (%) and verified through coaching and dietary recall. 2. Coaching call confirmation 3. Dietary recall cross-check	≥70% of provided child meals consumed per week during weeks 1–8, and ≥60% during the taper (weeks 9–12)
	The previous three sources will be used to calculate and confirm: • % of provided child meals consumed • % of family meals consumed	≥60% of provided family meals used per week
	A composite adherence score will be calculated (0-100 index each week; averaged across weeks)	Composite adherence score: High: ≥75 Moderate: 50–74 Low: <50
	Weekly Adherence Index = 0.50 × Child MTM uptake (%) + 0.20 × Family MTM uptake (%) + 0.30 × Coaching session completion (%)	
Progression criteria	Feasibility will be determined by whether the intervention meets at least 4 out of 5 of the defined feasibility progression criteria. For intervention adherence, criteria for adherence will be considered a composite score of 75 or greater. Meeting these progression criteria will support the decision to proceed to a future definitive trial.	

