#### Primary outcomes

2.7.1

Consistent with Mellor et al.’s recommendations for feasibility trials, we have defined specific progression criteria to determine whether the study procedures are practicable and whether to proceed to a larger trial [23].•**Recruitment feasibility (≥3 dyads/month):** This benchmark is informed by recruitment rates achieved in prior studies at the participating clinical sites and reflects both available research staff capacity and the anticipated burden on caregivers of children undergoing cancer treatment. Recruitment rates below this threshold may suggest limited reach, acceptability, or scalability of the intervention in its current form.•**Retention (≥75%) and assessment completion (≥85%) feasibility:** At least 75% of enrolled participants are expected to complete post-intervention assessments at 8 weeks, and at least 85% of participants retained at that time point should provide valid data for each assessment measure. These thresholds are consistent with feasibility and pilot study guidance indicating that retention rates of approximately 70-80% are generally required to support progression to a larger trial, particularly in vulnerable populations [21,24,25]. High assessment completion among retained participants will further indicate that study procedures are acceptable and not unduly burdensome.•**Intervention Adherence:** Adherence to the intervention will be evaluated as part of feasibility outcomes. For caregiver coaching, adherence will be defined as the proportion of scheduled sessions completed (target ≥75%). This threshold aligns with criteria used in similar behavioral interventions, where attending at least 75% of sessions is associated with increased retention of nutrition knowledge and meal behavior change. Weekly adherence will be derived from caregiver-completed meal adherence surveys, including reasons for missed meals. During weeks 1-8, categorical responses will be converted to estimated meal counts using pre-specified midpoint scoring rules. During weeks 9-12, numeric responses will be scored directly. These values will be converted to weekly MTM uptake percentages. Coaches will corroborate uptake during calls, and dietary recalls (ASA24) will include a tag to identify days when MANNA meals were consumed. MTM adherence will be summarized as the proportion of provided meals consumed (target ≥70% uptake during weeks 1–8 and ≥60% during taper weeks 9–12). These adherence metrics will be analyzed descriptively and used to interpret feasibility, acceptability, and exploratory clinical outcomes.•**Acceptability**: Domain scores (Meals, Coaching, and Overall/Integration) will be calculated as the mean of relevant items, and an overall acceptability index will be computed as the mean of all items. In alignment with feasibility benchmarks, the median score of the global item (“The overall Food-as-Medicine program was acceptable to me and my family”) will also be reported, with a threshold of ≥4 indicating strong acceptability. Additional questions will be asked, including if and how the meals affected family's daily routine, favorite and least favorite meals, and the most common reasons for child refusal of meals, among others. Both mean (SD) and median (IQR) values will be presented to characterize response distributions, and open-ended questions will provide qualitative insights to contextualize survey findings (Table 3).

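### The composite cut of 75 that decides adherence does not match the component targets in the same table: just meeting every target gives about 68 and fails, while 75 can be reached with child uptake below its weeks 1–8 target

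*Protocol article*

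**What the plan says.** Section 2.7, Table 2, lists several entries as criteria for intervention adherence:

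- Coaching: "≥75% of coaching sessions completed".
- Child meals: "≥70% of provided child meals consumed per week during weeks 1–8, and ≥60% during the taper (weeks 9–12").
- Family meals: "≥60% of provided family meals used per week".
- A composite: "A composite adherence score will be calculated (0-100 index each week; averaged across weeks"), banded High (75 or more), Moderate (50–74) and Low (under 50).

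The formula is "Weekly Adherence Index = 0.50 × Child MTM uptake (%) + 0.20 × Family MTM uptake (%) + 0.30 × Coaching session completion" (%). The progression row of the same table then names the deciding test: "criteria for adherence will be considered a composite score of 75 or greater". Progression needs at least four of the five criteria.

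Section 2.7.1 describes adherence by the coaching target of 75% and a meal target, "target ≥70% uptake during weeks 1–8 and ≥60% during taper weeks 9–12". It does not mention the composite, and it says the adherence metrics will be analysed descriptively.

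Two features of section 2.5 bear on the index. Coaching is bi-weekly in weeks 9–12, and families may opt out of the family meals. The article does not say how a week without a scheduled session, or a family that has opted out, enters the index.

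**The concern.** The component targets and the composite cut are both presented as criteria for one primary outcome, so they should agree on what adequate adherence is. The article neither derives 75 from the components nor says that it is meant to be a stricter bar. If they disagree, the plan can report adherence as not met when every listed component criterion is met, or as met when child meals, the most heavily weighted component, fall short. Someone working from 2.7.1 would also apply a different test from someone working from the progression row. With two conflicting standards in print, the choice between them could be made after the results are seen.

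**Working it through.** **Inputs (Table 2 and section 2.5).** Weights 0.50 child, 0.20 family, 0.30 coaching. Targets: child 70% (weeks 1–8) and 60% (weeks 9–12), family 60%, coaching 75%. Eight intensive and four taper weeks. Deciding cut 75. All uptake figures are programme averages.

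The article gives no derivation of 75, so there is no calculation of its own to reproduce. The check is whether the listed targets lead to it.

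**1. Every component exactly at target**

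- Weeks 1–8: 0.50×70 + 0.20×60 + 0.30×75 = 35 + 12 + 22.5 = 69.5
- Weeks 9–12: 0.50×60 + 0.20×60 + 0.30×75 = 30 + 12 + 22.5 = 64.5
- 12-week mean: (8×69.5 + 4×64.5)/12 = 814/12 = 67.8

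This is 7.2 points short of 75 and in the Moderate band.

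**2. Does unstated scoring rescue it?** Bi-weekly coaching leaves two of the four taper weeks without a session. One change at a time:

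| Handling | 12-week mean |
|---|---|
| Coaching carried at 75% in every week | 67.8 |
| No-session weeks: coaching dropped, weights rescaled, (30+12)/0.7 = 60 | (556+129+120)/12 = 67.1 |
| No-session weeks: coaching scored 0, 30+12 = 42 | (556+129+84)/12 = 64.1 |
| No-session weeks: coaching scored 100, 30+12+30 = 72 | (556+129+144)/12 = 69.1 |
| Opt-outs: family part dropped, weights rescaled, 57.5/0.8 = 71.875 and 52.5/0.8 = 65.625 | (575+262.5)/12 = 69.8 |

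Combining the two most favourable choices (all families opted out and rescaled, no-session weeks scored 100, so (30+30)/0.8 = 75 in those weeks) gives (575 + 131.25 + 150)/12 = 71.4. None reaches 75.

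**3. What passing takes**, coaching scored in every week

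- Family 60%, coaching 75%: child = (75 − 12 − 22.5)/0.50 = 81% on average.
- Child at target (mean (8×70 + 4×60)/12 = 66.7%) and family 60%: coaching = (75 − 33.33 − 12)/0.30 = 98.9%.

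**4. The other direction**, child uptake held constant over 12 weeks

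- Child 60%, family 90%, coaching 90%, scored every week: 30 + 18 + 27 = 75. This passes as High, 10 points under the weeks 1–8 child target.
- With family and coaching still at 90%, the lowest passing child uptake is 62% if no-session weeks are rescaled: 10(0.5c + 45) + 2(0.5c + 18)/0.7 = 900. It is 69% if they are scored 0: 10(0.5c + 45) + 2(0.5c + 18) = 900. Both are still under 70%.
- Boundary: child 50%, family 100%, coaching 100% gives 25 + 20 + 30 = 75. Rescaled or scored 0, that case gives 73.2 or 70.0 and fails; the lowest passing child uptake is then about 53% or 60%.
- Coaching can fall too: with child and family at 100% and coaching scored every week, (75 − 70)/0.30 = 16.7% suffices.

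**The case against.** The best defence is that the progression row says plainly which rule decides, so the plan can be applied without ambiguity. Section 2.7.1 calls the component figures targets and treats the metrics descriptively, and a composite may legitimately be set above the floors of its parts. This stands in part: the rule is operable, and the fault is an unexplained mismatch of thresholds. But strictness cannot account for step 4, where the composite is more lenient than a component target. It is a different test, not simply a tighter one.

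A reader might infer more than the documents support:

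- **That any programme meeting all its targets fails.** It does not. The targets are minimums. Child 80%, family 70%, coaching 85% gives 40 + 14 + 25.5 = 79.5 and passes. Only a programme at or near the floors fails.
- **That the plan generally accepts children eating half the meals.** The 50% figure is an extreme boundary. It needs complete family use and full coaching credit even in taper weeks without a session. Against the 60% taper target the shortfall is 10 points, not 20. Child uptake is also reported separately, so it would be visible.
- **That the mismatch by itself blocks or triggers progression.** Four of five criteria suffice, and meeting them supports the decision to proceed rather than forcing it.

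**Conclusion.** The concern holds as a misalignment between the component targets and the deciding cut. Components exactly at target score 67.8, or 64.1 to 69.8 when one scoring choice is varied at a time, against a cut of 75. In reverse, 75 is attainable with child uptake below its weeks 1–8 target, at 60% to 69% when family use and coaching are both 90%, depending on how no-session weeks are scored.

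The overall verdict changes only when exactly one other criterion also fails. Adherence is nevertheless part of the primary objective and is reported as a primary outcome, so misclassifying it matters in its own right. The documents do not show that 75, rather than the component targets, is the error, only that the two do not fit together. The figures assume that uptake is averaged over the programme and that two taper weeks have no session. This should be fixed; it is not a fatal flaw.

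**What to change.** Before results are known, state one adherence rule in Table 2 and repeat it in 2.7.1. There are two workable forms:

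1. **Components decide.** Judge the criterion on the listed component targets and report the composite descriptively.
2. **Composite decides.** Reconcile the cut with the component targets and also require child uptake to meet its own target. If those targets stand, the matching cut is about 68. If 75 is deliberately stricter, say so and align the targets with it. A child-uptake requirement alone still lets coaching be offset by meals, so say whether that is intended.

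If a composite is kept, specify how taper weeks without a session and family-meal opt-outs enter the index. The matching cut moves with both (64.1 if no-session weeks score 0, 69.8 if opt-outs are rescaled).

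The cost is a few lines in the table and in 2.7.1, with no new data. The first form removes the 75 hurdle, so a programme at the floors would pass, and it is stricter on child meals because they can no longer be offset.

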#### Primary outcomes

2.7.1

Consistent with Mellor et al.’s recommendations for feasibility trials, we have defined specific progression criteria to determine whether the study procedures are practicable and whether to proceed to a larger trial [23].•**Recruitment feasibility (≥3 dyads/month):** This benchmark is informed by recruitment rates achieved in prior studies at the participating clinical sites and reflects both available research staff capacity and the anticipated burden on caregivers of children undergoing cancer treatment. Recruitment rates below this threshold may suggest limited reach, acceptability, or scalability of the intervention in its current form.•**Retention (≥75%) and assessment completion (≥85%) feasibility:** At least 75% of enrolled participants are expected to complete post-intervention assessments at 8 weeks, and at least 85% of participants retained at that time point should provide valid data for each assessment measure. These thresholds are consistent with feasibility and pilot study guidance indicating that retention rates of approximately 70-80% are generally required to support progression to a larger trial, particularly in vulnerable populations [21,24,25]. High assessment completion among retained participants will further indicate that study procedures are acceptable and not unduly burdensome.•**Intervention Adherence:** Adherence to the intervention will be evaluated as part of feasibility outcomes. For caregiver coaching, adherence will be defined as the proportion of scheduled sessions completed (target ≥75%). This threshold aligns with criteria used in similar behavioral interventions, where attending at least 75% of sessions is associated with increased retention of nutrition knowledge and meal behavior change. Weekly adherence will be derived from caregiver-completed meal adherence surveys, including reasons for missed meals. During weeks 1-8, categorical responses will be converted to estimated meal counts using pre-specified midpoint scoring rules. During weeks 9-12, numeric responses will be scored directly. These values will be converted to weekly MTM uptake percentages. Coaches will corroborate uptake during calls, and dietary recalls (ASA24) will include a tag to identify days when MANNA meals were consumed. MTM adherence will be summarized as the proportion of provided meals consumed (target ≥70% uptake during weeks 1–8 and ≥60% during taper weeks 9–12). These adherence metrics will be analyzed descriptively and used to interpret feasibility, acceptability, and exploratory clinical outcomes.•**Acceptability**: Domain scores (Meals, Coaching, and Overall/Integration) will be calculated as the mean of relevant items, and an overall acceptability index will be computed as the mean of all items. In alignment with feasibility benchmarks, the median score of the global item (“The overall Food-as-Medicine program was acceptable to me and my family”) will also be reported, with a threshold of ≥4 indicating strong acceptability. Additional questions will be asked, including if and how the meals affected family's daily routine, favorite and least favorite meals, and the most common reasons for child refusal of meals, among others. Both mean (SD) and median (IQR) values will be presented to characterize response distributions, and open-ended questions will provide qualitative insights to contextualize survey findings (Table 3).

**Table 3 tbl3:** Intervention acceptability survey domains and scoring.

Domain	Items	Sample Item	Scoring Approach
Overall Intervention	3	“The overall Food-as-Medicine program was acceptable to me and my family.”	Mean of items 1–3; also report median of the global item (Item 1) for feasibility benchmark (≥4 = acceptable).
Medically Tailored Meals (MTMs)	5	“The meals helped reduce the time and stress associated with meal planning and preparation.”	Mean of items 4–8 (1 = Strongly Disagree to 5 = Strongly Agree).
Caregiver Coaching	4	“The coaching sessions were useful for managing my child's nutrition during treatment.”	Mean of items 9–12.
Integration & Sustainability	3	“The combination of meals and coaching worked well together.”	Mean of items 13–15.
Burden & Accessibility	1	“Participation in the study did not feel overly burdensome to my schedule.”	Single item (Item 16), reported descriptively.
Total Acceptability Index	All 16	N/A	Mean of all completed items (≥75% completion required). Higher scores = greater acceptability.

Notes:-Each item uses a 5-point Likert scale: 1 = Strongly Disagree, 2 = Disagree, 3 = Neutral, 4 = Agree, 5 = Strongly Agree.- For all domains and the total index, both mean (SD) and median (IQR) will be reported.- Qualitative open-ended responses will supplement quantitative scoring to contextualize acceptability findings.•**Progression Criteria**: Feasibility will be determined by whether the intervention meets at least 4 out of 5 of the defined feasibility criteria. Meeting these criteria will support the decision to proceed to a future definitive trial.

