**Methods:**

This prospective, single-arm feasibility study will enroll 60 caregiver–child dyads (N = 120) recruited from three outpatient pediatric oncology clinics at a large children's hospital. The 12-week intervention includes an intensive phase (weeks 1–8) with weekly MTM delivery and caregiver coaching, followed by a tapered phase (weeks 9–12) with reduced meal frequency and bi-weekly coaching. Feasibility outcomes include recruitment, retention, assessment completion, intervention adherence, and acceptability, evaluated against predefined progression criteria. Exploratory outcomes will be assessed at baseline and at 3, 6, and 12 months post-intervention using validated dietary, anthropometric, clinical, and caregiver-reported measures.

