### Study population and sample size

2.2

In this study, caregiver-child dyads in which the child is actively receiving cancer treatment will be invited to participate in a food-as-medicine intervention. Consistent with the aims of early-phase research, this feasibility study is not powered to detect statistically significant intervention effects; rather, its primary purpose is to assess feasibility and acceptability and to generate data that will inform the design of a subsequent, fully powered trial. A total of 60 caregiver-child dyads (N = 120; 60 children and 60 caregivers) will be enrolled using convenience sampling.

This sample size is consistent with methodological recommendations for pilot and feasibility studies, which suggest that samples of approximately 50-60 participants are common and adequate for evaluating key feasibility outcomes such as recruitment, retention, intervention adherence, and acceptability, particularly when multiple feasibility indicators are of interest [21,22]. Prior reviews of feasibility studies report a median total sample size of approximately 60 participants and note that samples in this range are sufficient to characterize feasibility parameters with reasonable precision while minimizing participant burden and resource use [22]. The proposed sample will allow estimation of feasibility metrics and associated confidence intervals to guide progression criteria and inform planning of a future randomized trial.

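### The retention criterion is set at 8 weeks in section 2.7.1 but at 12 weeks in Table 2, no week-8 assessment is scheduled, and the follow-up clock needs one stated anchor

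*Protocol article*

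**What the plan says.** All references are to the protocol article.

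- **Retention, section 2.7.1:** "At least 75% of enrolled participants are expected to complete post-intervention assessments at 8 weeks". The assessment criterion follows from it: "at least 85% of participants retained at that time point should provide valid data for each assessment measure".
- **Retention, Table 2:** "Percent of participants providing assessment data at 12 weeks", with the same 75% threshold. Table 2 gives the assessment criterion among retained participants but no separate time point for it.
- **Intervention, section 2.5:** "The intervention is delivered over a 12-week period". Week 8 closes the intensive phase; the taper runs over weeks 9–12.
- **Visits, section 2.6:** four primary time points are listed, namely baseline and 3, 6 and 12 months. The same section says: "Post-intervention assessments will be conducted immediately following completion of the intervention period".
- **Visits, abstract:** "Exploratory outcomes will be assessed at baseline and at 3, 6, and 12 months post-intervention". Sections 2.6 and 2.7.2 use similar wording, attaching the post-intervention label to follow-up at 3, 6 and 12 months.
- **Table 1:** the 3-month visit comes directly after weeks 9–12 and has a window of +28 days only. The 6- and 12-month visits have ±28 days. No assessment visit falls at week 8.
- **Decision rule:** progression requires at least four of five criteria (Table 2, sections 2.7.1 and 2.8).

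**The concern.** Retention is one of the five progression criteria, and it supplies the denominator for a second one, assessment completion. The text that defines it names two different weeks for one threshold. One of those weeks falls during the intervention, although the sentence calls it post-intervention.

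The follow-up clock adds a second problem. If the first follow-up visit is 3 months after the intervention ends, as the abstract says, nothing is assessed at week 12 and Table 2's criterion has no data to draw on. If that visit is the end-of-intervention visit, the abstract is wrong. The acceptability survey is scheduled only at this visit, so three of the five criteria (retention, assessment completion and acceptability) depend on where it falls. With the wording unreconciled, the time point could be settled after the data are known.

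**Working it through.** **Inputs.** There are 60 enrolled dyads (section 2.2), a 75% threshold (Table 2 and section 2.7.1), candidate time points of week 8 (section 2.7.1) and week 12 (Table 2), and a 12-week intervention (section 2.5). The article gives no dropout rate or timing. The sample size is justified by convention, so there is no calculated figure to reproduce.

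**Step 1: the threshold as a count.** 0.75 × 60 = 45. At least 45 dyads must be retained, so at most 15 may be lost.

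**Step 2: can week 8 be scored?** For weeks 1–8, Table 1 lists record review, meals, coaching, the weekly meal adherence survey and adverse event reporting. The outcome assessments appear only at baseline and at 3, 6 and 12 months. No post-intervention assessment exists at week 8, so the section 2.7.1 criterion cannot be evaluated as worded.

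**Step 3: does the time point matter to the count?** This example needs no dropout model:

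- 14 lost by week 8: 60 − 14 = 46, and 46/60 = 76.7%, above the threshold.
- Two more lost in weeks 9–12: 46 − 2 = 44, and 44/60 = 73.3%, below it.

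The assessment denominator moves too. 85% of 46 is 39.1, so 40 are needed; 85% of 44 is 37.4, so 38 are needed.

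**Step 4: illustration under an assumed constant dropout hazard, with permanent dropout.** Let S(w) be the proportion retained at week w; then S(12) = S(8)^(12/8).

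- S(8) = 0.75 gives S(12) = 0.75^1.5 = 0.650, or 39 of 60.
- S(12) = 0.75 requires S(8) = 0.75^(8/12) = 0.825.

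A study with 45 or more at week 12 also had 45 or more at week 8. The chance of being above the threshold at week 8 and below it at week 12 is therefore the difference between two binomial tail probabilities with n = 60:

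| Retention at week 8 | Retention at week 12 | P(≥45) at week 8 | P(≥45) at week 12 | Difference |
|---|---|---|---|---|
| 78% | 68.9% | 0.768 | 0.190 | 0.58 |
| 80% | 71.6% | 0.869 | 0.333 | 0.54 |
| 82% | 74.3% | 0.938 | 0.516 | 0.42 |
| 85% | 78.4% | 0.986 | 0.789 | 0.20 |
| 90% | 85.4% | 1.000 | 0.989 | 0.01 |

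**Step 5: where is the 3-month visit?** Counted from the start, 3 months is about week 13, which matches the end of the intervention; the +28-day window takes a 12-week visit to week 16. Counted from the end, it is about 12 + 13 = week 25. Table 1's column order, its plus-only window and the single placement of the acceptability survey fit the first reading, as do section 2.6's assessment immediately after the intervention and Table 2's 12 weeks. The abstract states the second reading. The wording in sections 2.6 and 2.7.2 can be taken either way.

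**The case against.** The strongest reply is that the 8 is a slip in explanatory text. The sentence undermines itself by calling week 8 post-intervention, and section 2.8 cites Table 2 as the source of the predefined criteria. On that view there is one workable rule, at 12 weeks. Much of this stands. A reader might infer that two rules are in force and that the same dropout would pass under one and fail under the other. The documents do not support that, because no scheduled assessment could yield a week-8 result. What remains is that no passage corrects the figure, and section 2.7 points both to the text below it and to the tables as describing the primary outcomes.

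The visit clock is also less open than the abstract suggests, given the layout of Table 1. A reader might infer that the anchor alters every pre–post summary and every variance estimate for the next trial. That would follow only if the less supported reading were adopted, and those outcomes are exploratory and descriptive.

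A reader might also see a second conflict between completing assessments (section 2.7.1) and providing assessment data (Table 2). This is not shown: section 2.7.1 separates being retained from giving valid data on each measure, so completing there need not mean every measure is valid.

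Finally, the hazard figures rest on an assumption that the article does not supply. At 90% retention in week 8 the criterion is almost certainly met at both times.

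**Conclusion.** The point holds as an internal inconsistency that has to be corrected. The 8-week time point in section 2.7.1 is wrong as written. It conflicts with Table 2, falls inside a 12-week intervention, and matches no assessment in Table 1; the denominator of the 85% criterion inherits the error. The abstract's clock conflicts with section 2.6 and, taken literally, leaves the 12-week criterion without a visit, although Table 1 favours the 3-month visit as the end of intervention.

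The size is modest and conditional. The threshold is 45 of 60 at either time, and losses in weeks 9–12 matter only if they carry the count across 45. The probabilities above, from 0.58 down to 0.01, depend on a constant hazard and on the assumed week-8 retention. Under the 4-of-5 rule, a reversal in retention alone changes the decision only when exactly three of the other four criteria are met. If all four are met, the study progresses either way; if two or fewer are met, it does not.

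**What to change.** 1. In section 2.7.1, replace the 8-week time point with the 12-week end-of-intervention visit, to match Table 2. The 85% criterion then takes its denominator from that visit.
2. State in Table 1 and section 2.6 that the 3-month visit is this visit, with its +28-day window, and refer to it in the same terms in Table 2.
3. Reword the post-intervention label in the abstract and sections 2.6 and 2.7.2 so that all visits run on one stated clock. The article does not name the starting event of that clock; the sponsor should name it.

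The cost is wording only, with no added visit and no change to the threshold. Retention at week 12 may come out slightly less favourable than a week-8 figure would have. The registry record was not available, so whether it needs the same correction is not known. The change should be made before retention data are seen.
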